## Abstract

**Background:**

Anthrax is a major but neglected zoonotic disease of public health concern in India with Odisha contributing a major share to the disease burden. *Bacillus anthracis* spores can be found naturally in soil and commonly affect both animals and humans around the world. Domestic and wild animals such as cattle, sheep, goats, and deer can become infected when they inhale or ingest spores from contaminated soil, plants, or water. Anthrax can be fatal if patients are not treated promptly with antibiotics. This protocol aims to describe the implementation and evaluation of the ‘One Health’ intervention model based on the principles of Theory of Change (ToC) to eliminate human anthrax from a tribal district in Odisha, India.

**Methods:**

This study would test the effectiveness of a complex public health intervention package developed using the ToC framework for the elimination of human anthrax in Koraput district by a comparative analysis of baseline and end-line data. We plan to enroll 2640 adults across 14 geographically divided blocks in Koraput district of Odisha for baseline and end-line surveys. After baseline, we would provide capacity building training to stakeholders from the department of health, veterinary, forest, academic and allied health institutions followed by workshops on sensitization and awareness through IEC (Information Education Communication)/BCC (Behavior Change Communication) activities in the community. We would establish a state-level laboratory facility as a robust system for timely diagnosis and management of human anthrax cases. Surveillance network will be strengthened to track the cases in early stage and risk zoning will be done for focused surveillance in endemic areas. Advocacy with district level administration will be done for maximizing the coverage of livestock vaccination in the entire district. Interdepartmental coordination would be established for the effective implementation of the intervention package.

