### Sample size determination

The sample size required for the quantitative component of the baseline (and end-line) study was estimated to be 2608. For uniformity of sampling, this was rounded off to 2640 in total. This was calculated by the following formula:
$$\text{The}\;\text{minimum}\;\text{sample}\;\text{size}\;\text{required}=\frac{\left[(1.96{)}^{z}*P*(1-P)\right]}{d^{2}}*(\text{Design}\;\text{effect})$$
Where the level of confidence assumed at 95%, corresponding to Z = 1.96; P = Prevalence of high-risk exposure to anthrax (Assumed at 5%); d = Relative precision at 20% of P; Design effect = 1.3; Non-Response rate = 10%. For the qualitative component, data collection would be continued until saturation is reached based on the principle of maximum divergence [20].

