### Data analysis

Effectiveness of our complex public health intervention package will be analyzed as a whole One Health strategy instead of its separate components for elimination of human anthrax cases in endemic regions. Furthermore, the impact of each intervention will be tracked through the logic model developed by us with different levels such as inputs, activities, outputs, indicators, outcomes & impact [Table 4 in S3 Appendix]. Our quantitative and qualitative surveys during baseline and end line will be analyzed to observe the effectiveness of implementation of our intervention package and to observe the improvement in knowledge, behavior, and practices with regards to the anthrax disease among communities residing in the Koraput district. Annual data of animal vaccination, animal and human anthrax cases and deaths will also be an analysis to see the progress and track the effective implementation of our intervention package. The data of human anthrax cases and deaths will be taken from IDSP (Integrated Diseases Surveillance Program) Odisha and similarly the data of animal vaccination coverage, animal anthrax cases and deaths will be taken from Veterinary department in the district. At the end of the 3 years, we will do a comparative analysis of vaccination coverage, animal and human anthrax cases and deaths in the district to find the effectiveness of our interventions. Descriptive statistics will be used for the analysis of quantitative data though SPSS (Statistical Package for Social Sciences) or STATA. Qualitative data will be analyzed through thematic analysis, and network diagrams. The primary comparison of baseline and end-line data will be made by applying tests of statistical significance where applicable, with a level of significance established at p = 0.05. Moreover, bottleneck analysis will be done using appropriate models for the surveillance system in place and finding of this study will be published in open access journal upon completion of study [23].

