## Discussion

The study is for three years based on implementation models including surveys (baseline and end line), capacity building, and sensitization of various stakeholders from the department of health, veterinary, and forest systems at various levels in a tribal district of Odisha, India. The prevalence and outbreaks of anthrax are interlinked with the animal-environment-human context, which signifies the need for collaborative, transdisciplinary, and multi-sectoral approaches for the prevention and control of anthrax [24]. The intervention builds upon a preliminary study to strengthen the health care and surveillance system for early reporting of suspected cases of human and animal anthrax by developing and implementing the “One-Health” strategy. We aim to eliminate incidences of human anthrax cases to zero by the end of three years using a multi-sectoral team-based approach. We also propose for sustainable on-ground investigation and surveillance after this intervention-implementation in collaboration with health, veterinary, forest and other allied departments in the district and state. Effectiveness of the capacity building training for enhancing knowledge will be assessed by structured pre- and post-assessments. Findings from this study would provide recommendations for policymaking and future scale-up planning to the elimination of zoonotic diseases using ‘One Health’ strategies. Moreover, the study protocol may further be replicated in other endemic regions of India as well as other countries.

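### The elimination claim is attached to the baseline/end-line surveys, which hold about 0.1 reported anthrax cases a year; the planned district case comparison should carry it

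*Protocol article*

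**What the plan says.** The Abstract (Methods) states that the intervention package is tested "for the elimination of human anthrax in Koraput district by a comparative analysis of baseline and end-line data". The next sentence ties both time points to the surveys: "We plan to enroll 2640 adults across 14 geographically divided blocks in Koraput district of Odisha for baseline and end-line surveys". The Data analysis section then says "The primary comparison of baseline and end-line data will be made by applying tests of statistical significance where applicable", at a significance level of 0.05. In Table 2, baseline and end-line appear only as surveys.

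Under Sample size determination, the survey is sized to estimate the prevalence of high-risk exposure, assumed at 5%, with "d = Relative precision at 20% of P". Participant selection and Table 3 describe its content: demography, livestock, vaccination, animal handling, food habits, and knowledge of and experience with anthrax.

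The Data analysis section also plans to take human cases and deaths from IDSP, and to compare cases, deaths and vaccination coverage in the district after three years in order to judge effectiveness. The Discussion sets the target: "We aim to eliminate incidences of human anthrax cases to zero by the end of three years".

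**The concern.** Two comparisons are planned, and the one labelled primary is not the one that can speak to elimination. The surveys measure what people know and do. The IDSP series measures human anthrax. Read together, the Abstract and Data analysis attach the elimination test to the surveys and leave the IDSP comparison without a rank.

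The study has a single arm, and its results are meant to guide policy and replication elsewhere. As the text stands, a significant gain in knowledge or practice could be reported as effectiveness for elimination. That would be an inference from behaviour to disease which the survey data cannot check.

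**Working it through.** **1. What the survey is sized for.** Inputs from Sample size determination: z = 1.96, P = 0.05, d = 0.20 × 0.05 = 0.01, design effect 1.3, non-response 10%. The exponent printed as z is taken as 2.

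- 1.96² × 0.05 × 0.95 / 0.01² = 1824.8
- × 1.3 = 2372.2
- × 1.10 = 2609.4 (dividing by 0.90 instead gives 2635.8)

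The stated 2608 is reproduced to within 2. It is a precision calculation for one exposure prevalence. No anthrax case rate enters it.

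**2. Cases expected in the sample.** Inputs: more than 300 human cases over 6 years (Background) and 1.37 million residents (Study setting).

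- 300 / 6 = 50 reported cases a year
- 50 / 1,370,000 = 3.65 per 100,000 a year
- 2640 × 50 / 1,370,000 = 0.096 reported cases a year
- chance of no case in a one-year window with no intervention effect: exp(−0.096) = 0.91

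**3. What a survey comparison could detect.** Suppose end-line shows no case at all. With equal samples, an exact two-sided test on k baseline cases against 0 gives p = 2 × 0.5^k, which is 0.063 for k = 5 and 0.031 for k = 6. At least 6 baseline cases are needed, against 0.096 expected. By a normal approximation (crude at such counts), power for a fall to zero is about 5%, no more than the significance level, and about 215,000 people per survey would be needed for 80%.

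**4. Sensitivity to under-reporting.** The Background says many cases go unreported but gives no factor, so a range is assumed. If true cases were 10 times those reported, and the survey captured them all, 0.96 would be expected a year and power would be about 16%. Roughly 80-fold under-reporting would be needed for about 80% power.

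**5. What the district series can show.** At about 50 reported cases a year, the IDSP count can show a fall. A zero still needs care, because cases come in outbreaks. For zero events in one year, the one-sided 95% Poisson limit is −ln(0.05) = 3.0 events. If the independent event is an outbreak, that is 3 outbreaks a year, not 3 cases. The documents give no outbreak size, so three are assumed:

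| Mean cases per outbreak (assumed) | Outbreaks a year at 50 cases | Chance of an outbreak-free year with no effect | Cases a year compatible with zero outbreaks |
|---|---|---|---|
| 10 | 5.0 | exp(−5.0) = 0.7% | 30 |
| 15 | 3.3 | exp(−3.3) = 3.6% | 45 |
| 25 | 2.0 | exp(−2.0) = 13.5% | 75 |

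**6. Timing.** Table 2 schedules implementation from the second half of Year 1 to the end of Year 2, and the end-line survey in the first half of Year 3. The zero target is set for the end of three years, so the end-line survey comes before the point at which it is to be judged.

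**The case against.** The strongest reply is that the right data are already in the plan. The Data analysis section commits to comparing IDSP human cases and deaths after three years to find effectiveness, gives the surveys the job of tracking knowledge, behaviour and practice, and never says that the surveys will count cases. The phrase about baseline and end-line data is not expressly limited to surveys. On this view only a label is loose.

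Much of this stands, and it rules out several stronger readings that a reader might infer:

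- *That the study has no means of addressing elimination.* It has: the IDSP comparison.
- *That the surveys cannot observe anthrax at all.* Table 3 includes self-report items on recent cases and on experience with human anthrax. The limit is the tiny expected number, with no diagnostic testing listed in that table.
- *That the primary comparison fails the primary objective.* The Objectives section makes developing and implementing the package, to demonstrate a replicable elimination strategy, the primary aim and lists effect on burden as secondary.
- *That no observation window or decision rule exists.* One may sit in the logic model in S3 Appendix, the full protocol or an analysis plan, none of which is shown.
- *That under-reporting is ignored.* The Background acknowledges it, and the package includes surveillance, a diagnostic facility and case definitions.

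What does not fall away is the assignment itself. The Data analysis section speaks of surveys at baseline and end line but calls the case counts annual data. The Abstract places the elimination test on baseline and end-line data and follows it with the 2640-adult surveys. This is what the article states, not a detail that it left out.

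**Conclusion.** The point holds as a misassignment of the elimination claim. The comparison called primary rests, as the article uses its terms, on surveys that would hold about 0.1 reported cases a year and would show none about 91% of the time with no effect. A significant survey p-value cannot support elimination. The IDSP human case series can bear on it, and is planned, but is not named as the primary comparison.

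The figures assume that the reported rate applies evenly across the district and all ages, and they use 300 cases, which is a lower bound. Tenfold under-reporting does not change the conclusion. The outbreak sizes and under-reporting factors are assumptions. A reader might want a rule such as zero cases over 12 months. Nothing in the documents supplies it, and by itself it would not exclude a chance outbreak-free year.

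**What to change.** - **Abstract (Methods) and Data analysis:** name district human anthrax incidence from IDSP, pre-project years against Year 3 (the period after implementation ends in Table 2), as the outcome for the elimination or effectiveness claim. State that the survey comparison addresses knowledge, behaviour and practice only.
- **Data analysis:** report any zero count with an upper confidence limit computed on outbreaks rather than independent cases. Give the number of suspects tested in each period beside it, because the package itself strengthens case detection and so changes ascertainment between the periods compared.
- **Discussion:** describe a result short of sustained zero as a reduction. If S3 Appendix or the full protocol already defines the observation window for zero, cite it; if not, the investigators should set and justify one.

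The cost is a few sentences, slightly more analysis and a more modest claim. The IDSP case data are already planned; the numbers of suspects tested would have to be obtained from surveillance or laboratory records, if these are kept for the pre-project years.

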**Conclusion:**

This would be a first study applying One Health concept for the elimination of human anthrax in India. The findings from this study will offer important insights for policy-making and further replication in other endemic regions of the state and country.

**Trial registration:**

The authors confirm that all ongoing and related trials for this intervention are prospectively registered with the Clinical Trials Registry of India [CTRI/2020/05/025325] on 22 May 2020.

## Background

Zoonoses are recognized as a major concern in developing nations, in need of a resolution [1]. It is commonly agreed that the detection, management, and elimination of zoonotic diseases requires joint efforts from the animal and human health sectors [2, 3]. Joint monitoring systems such as “One Health” strategy are the most efficient and reliable means of addressing zoonotic diseases such as anthrax in low-income countries [4]. Most of these countries are lacking an integrated control system to address gaps across human health, animal health, food and environment sectors with limited collaborative works. As a result, elimination of a zoonotic diseases remains an unsuccessful goal due to the lack of specific investigation protocol, insufficient knowledge and weak coordination among the responsible stakeholders [5]. The One Health approach mainly relies on vigorous examination of evidence for proof of concept which can be achieved through in-person meetings, circulation of meeting summaries and establishment of standard operating procedures. This concept is already found to have significance when implemented to tackle the newly emerging diseases like Middle East respiratory syndrome, avian flu (H5N1), swine flu (H1N1), Ebola and Zika virus [6, 7]. Management and effective control of anthrax through One Health concept is described as a highly demanding approach although it needs a robust implementation globally [8].

Zoonotic diseases have a significant impact on India’s public health, animal economies, and wildlife. Among these diseases, anthrax contributes to most cases [9]. Anthrax is a widespread zoonotic disease that mainly affects herbivorous animals, triggered by rod-shaped, gram-positive bacteria known as *Bacillus anthracis*. [10, 11] Anthrax most often arises in warm-blooded wild or domesticated livestock such as sheep, cattle, and goats but can cause disease in humans, inducing three forms of the lung (pulmonary), digestive (intestinal), or skin (cutaneous) infections. Ultimately all forms of anthrax may spread across the body and cause death if not properly treated with antibiotics at the right time. Anthrax is known to be a hot-season disease and outbreaks continue to occur in hot-dry climates accompanied by occasional brief showers [12].

India is an endemic country for animal anthrax owing to a large and unsafe population of livestock leading to the outbreaks of human cases in certain parts [13, 14]. In many states of India, anthrax is enzootic including Andhra Pradesh, Jammu and Kashmir, Tamil Nadu, Odisha, and Karnataka [15]. The real burden of anthrax in India is not understood precisely since a significant number of cases go unreported and only a portion of human cases seek medical care [16].

Over the last 15 years, 14 districts out of 30 revenue districts in Odisha have experienced outbreaks of human anthrax with 1208 cases and 436 deaths [17, 18]. Among those affected districts, Koraput has more than 300 human anthrax cases including 10 deaths over the past 6 years. Almost all the cases came from a group of indigenous tribes involved in handling and consuming animal carcasses. Therefore, this implementation research project is planned in the district of Koraput using the "One Health" approach to demonstrate the feasibility for the elimination of human anthrax cases in three years.

### Objectives

The primary objective of this study is to develop and implement a package of coordinated interventions using the “One Health” approach to demonstrate a replicable strategy for the elimination of animal-to-human disease transmission of anthrax in an endemic district of Odisha.

Secondary objectives include assessment of disease burdens, patterns, knowledge, prevalence, and practices among the identified stakeholders from the departments of health, animal husbandry, environment/forest, and the community; and to evaluate the effectiveness of the interventions among the study population on anthrax burden in the study district along with cost-benefit analysis of interventions.

## Methods

### Study design

This is an implementation-effectiveness hybrid design implementation research with a single-arm interventional study built-in to test the effectiveness of structured public health interventions. This includes a phase of formative research including mapping of the project area, development of intervention packages using “Theory of Change” principles and preparing communities & stakeholders for the planned interventions. Phase II entails the implementation and evaluation of the intervention package, using an iterative process of community trials. Qualitative methods would be used to evaluate the feasibility and acceptability of the interventions among the implementers and target population.

### Study setting

This study will be carried out in the Koraput District (which has a population of 1.37 million residents across 2028 villages) reporting the highest number of human anthrax cases in Odisha state [18, 19]. Within the district, it will be executed in all geographically divided 14 administrative blocks, which comprise 240 village administrative bodies or ‘gram panchayats’; this includes many tribal villages based in hilly areas [Fig 1]. Eight villages from each block were selected randomly for baseline and end-line assessment surveys of the community trials.

**Fig 1 pone.0251041.g001:**
[figure not shown]
Study setting map.

### Study participants

Participants will be enrolled by following the inclusion and exclusion criteria given below:–

Inclusion criteria: Participants will be selected based on the eligibility criteria: a) Should be an adult (age above 18 years) and a permanent resident of Koraput district, b) willing to participate in the study.Exclusion criteria: a) Cognitive impairment, b) having onset symptoms or infected with any of the communicable disease which can be spread through nasal or mouth droplets.

The study participants for the baseline and end-line study will be sampled from the stakeholders identified in the district. A comprehensive stakeholder mapping and analysis will be carried out based on the broad categories outlined in [Table 1].

**Table 1 pone.0251041.t001:** Identified groups of stakeholders to be included in the study.

Health Care Sector	Animal Care Sector	Community
**Clinical service providers**	Veterinary doctors	Service utilizer clients
**Program managers**	Livestock inspectors	Local governance members
**Health workers**	Forest guards	Non-governmental organizations and Self-help groups
**Accredited social health activists (ASHAs)**		Cattle owners/grazers
		Hunter/gatherers
		Village residents

Additionally, participants for the qualitative study will be selected purposively from the known hotspots of outbreaks and tribal communities with practices that make them vulnerable for anthrax infection, acquisition, and propagation.

### Sample size determination

The sample size required for the quantitative component of the baseline (and end-line) study was estimated to be 2608. For uniformity of sampling, this was rounded off to 2640 in total. This was calculated by the following formula:
$$\text{The}\;\text{minimum}\;\text{sample}\;\text{size}\;\text{required}=\frac{\left[(1.96{)}^{z}*P*(1-P)\right]}{d^{2}}*(\text{Design}\;\text{effect})$$
Where the level of confidence assumed at 95%, corresponding to Z = 1.96; P = Prevalence of high-risk exposure to anthrax (Assumed at 5%); d = Relative precision at 20% of P; Design effect = 1.3; Non-Response rate = 10%. For the qualitative component, data collection would be continued until saturation is reached based on the principle of maximum divergence [20].

### Ethics approval and consent to participate

The institutional review board of the ICMR—Regional Medical Research Centre, Bhubaneswar approved this study. The Indian Council of Medical Research has reviewed and approved the study design and protocols. All participants will receive written information on study aims, participation requirements, and the right to refuse. Furthermore, they will complete the written informed consent process before participation.

### Theoretical framework

We would use the Theory of Change (ToC) principle to build and test the complex intervention model for the said objectives. Theory of Change articulates the change process and describes how interventions can bring about long-term outcomes through a logical sequence of intermediate outcomes [21]. Thus, we have adopted this concept to empower and enable the various stakeholders to build interventions to bring about behaviour change among community members and systems. ToC frameworks emphasize on how a complex intervention interacts with the wider system rather than being considered only in the context of one sector [18].

